# GoPerio - impact of a personalized video and an automated two-way text-messaging system in oral hygiene motivation: study protocol for a randomized controlled trial

**DOI:** 10.1186/s13063-019-3738-0

**Published:** 2019-12-10

**Keywords:** Oral hygiene, Motivational interviewing, Patient education as topic, Patient Compliance, Video, Text messaging, Periodontal diseases, Dental plaque, Telemedicine, eHealth

## Abstract

**Background:**

Oral hygiene is of paramount importance for the preservation of oral health, and for patients affected by periodontal disease establishing an effective oral hygiene routine is the first step of therapy. Several clinical frameworks have been developed to foster behavior change, such as motivational interviewing. However, two obstacles can be identified. First, patients tend to forget the advice they were given during the consultation. Second, it is hard to maintain motivation in the long term, thus leading to relapse. An innovative eHealth solution was designed with the aim to tackle both obstacles and supplement the current clinical standard of care. The primary objective is to compare the full mouth plaque scores of study groups (eHealth plus standard of care versus standard of care only) at 8 weeks of follow up. The main secondary objective is to compare the full mouth bleeding score at 8 weeks of follow up.

**Methods/design:**

The “GoPerio” study is a multicenter, randomized, controlled trial assessing the impact of a novel eHealth concept for oral hygiene motivation (personalized video of oral hygiene routine available for the patient via a cloud server plus interactive text messages) in addition to the current standard of care (motivational interviewing plus tooth scaling and polishing). The minimum sample size required is 86 patients. Participants will be randomized (allocation ratio 1:1): test group (eHealth plus standard of care) versus control group (standard of care only). The primary outcome is oral hygiene as measured by the full mouth (six sites per tooth) plaque control record (PCR) index. The main secondary outcome is gingival inflammation as measured by the full mouth (six sites per tooth) bleeding on probing (BOP) index. Both the primary and the main secondary outcomes are evaluated by blinded and calibrated examiners at 8 weeks of follow up. The other secondary outcomes are patient satisfaction and patient behavior change and motivation.

**Discussion:**

The study will investigate the value of an innovative eHealth approach to strengthen patient motivation for oral hygiene. If proven effective, such an approach would supplement the current clinical standard of care, resulting in improved clinical outcomes with negligible impact on productivity in a dental practice.

**Trial registration:**

ClinicalTrials.gov, NCT03109808. Registered on 12 April 2017.

Sponsor: Hospices Civils de Lyon. [name].

Protocol version**:** 1.0 as of 21 September 2016.

## Background

Dental plaque is a bacterial biofilm that is responsible for most periodontal diseases when there is dysbiosis of the oral ecosystem, often due to a lack of oral hygiene [1]. The two main periodontal conditions are gingivitis and periodontitis [2]. In the experimental model of gingivitis, if oral hygiene is reinstated, inflammation is reduced and tissues heal *ad integrum* [3]. If left untreated and compounded by other factors (genetic, environmental, local, etc.), gingivitis evolves to periodontitis in susceptible people [4–6]. In addition to gum inflammation, periodontitis leads to a deeper destructive process targeting the tooth-supporting tissue such as the alveolar bone. Ultimately, this irreversible tissue destruction can lead to the loss of teeth [7]. Other well-documented risk factors for periodontitis include smoking and diabetes mellitus [5, 8–10].

A key aspect of periodontal therapy is the instruction and motivation of patients for a satisfactory level of oral hygiene. Once oral hygiene is established, non-surgical and surgical periodontal care can be initiated. In adults, twice daily toothbrushing and daily interdental care (dental floss or interdental brushes) considerably reduces the amount of dental plaque accumulated on teeth [11–13]. Adequate plaque control reduces the prevalence and the severity of periodontal diseases [14]. It reduces the risk of tooth loss both in healthy patients [15] and in those enrolled in supportive periodontal therapy [16].

Several frameworks have been proposed to improve oral hygiene in periodontal patients, among which one can differentiate those that rely mostly on patient education, those that emphasize the use of technology, and those that combine patient education theories and the use of technology. Behavior change techniques can be used by the practitioner to enhance a patient’s motivation for durable oral hygiene and healthy habits [17]. One such technique is motivational interviewing (MI), a patient-centered communication technique [18]. MI has been successfully implemented in patient motivation in periodontology [19–22] and in smoking cessation advice [23]. Researchers have also proposed several solutions taking advantage of technology. Videos for oral hygiene instruction have not shown any difference when compared to a clinical consultation [24, 25], but the videos in these studie were pre-recorded and generic (i.e. non-personalized). Conversely, having a personalized video filmed by the dentist or the dental hygienist during the consultation, displaying all steps for a correct oral hygiene routine, could be worth exploring as patients may relate more easily to images of their own teeth. Frequent recalls have also been shown to increase long-term adherence in patient motivation for oral hygiene [26, 27], and it is of note that for chronic diseases text-message-based recalls improved adherence to medication in several trials [28–32].

It is possible to combine patient motivation techniques and technological aspects to create innovative eHealth solutions. eHealth is defined as an “emerging field in the intersection of medical informatics, public health and business, referring to health services and information delivered or enhanced through the Internet and related technologies” [33]. The eHealth concept proposed and evaluated in this randomized controlled trial (RCT) features three key aspects: a consultation taking advantage of MI, personalized oral hygiene videos accessible anytime on a smartphone via a cloud portal, and regular and interactive text messages to enhance patient adherence to the oral hygiene routine. To the best of the authors’ knowledge, such a strategy has yet to be evaluated in a RCT.

### Objectives and hypotheses

The aim of this randomized trial is to evaluate an eHealth concept for patient motivation for oral hygiene through the combined use of MI, a personalized oral hygiene video, and motivational interactive text messages.

The primary objective is comparison of the level of oral hygiene as assessed by plaque scores (that range from 0 to 100%) in individuals who benefited from the control versus test patient education strategies at 8 weeks. The main secondary objective is the gingival inflammation as assessed by bleeding on probing (BOP) index (the values of which range from 0 to 100%) of the control and test groups at 8 weeks. Two secondary objectives will be also considered: the satisfaction after 8 weeks and patient motivation for change after 4 and 8 weeks in each treatment arm. Interventions are subsequently further defined.

The underlying hypothesis is that the eHealth concept for patient motivation for oral hygiene would allow better instruction and motivation for oral hygiene because it gives patients constant access to a video summarizing their oral hygiene routine, and patients benefit from regular contact via text messages.

## Methods

### Trial design

The Standard Protocol Items: Recommendations for Interventional Trials (SPIRIT) statement [34] and SPIRIT - Patient-reported Outcomes (SPIRIT-PRO) extension [35] (for patient-reported outcomes) were taken into account in the design of the present clinical trial.

This is a multicenter, randomized controlled trial with two parallel arms. For the primary objective and secondary objectives, only outcome examiners and data analysts are blinded to the allocated intervention (control or test patient education strategy). Patients are randomized at the end of the first consultation so that patients and investigators are not aware of the allocation during the patient education and motivation procedure.

Patients are randomized (allocation ratio 1:1) for the type of patient education strategy (control versus test) with stratification based on center of inclusion, patient gender (male versus female), and tobacco status (currently using tobacco versus currently not using tobacco).

The flow chart of the study is presented in Fig. 1. The schedule of enrollment, intervention, and assessment is reported according to the SPIRIT statement (Fig. 2). The content of each visit is summarized in Fig. 3.

**Fig. 1 Fig1:**
[figure not shown]
Flow chart. ^1^ PCR = plaque control record. ^2^ BOP = bleeding on probing. ^3^ DVSS = dental visit satisfaction scale

**Fig. 2 Fig2:**
[figure not shown]
Schedule of enrollment, interventions, and assessments. eCRF, electronic case report form

**Fig. 3 Fig3:**
[figure not shown]
Content of the study visits. ^1^ PCR = plaque control record. ^2^ BOP = bleeding on probing. MI, motivational interviewing

### Setting and participants

This study is carried out in two teaching hospitals, one located in France and the other in Belgium: the dental teaching hospital of the Lyon university hospitals (Lyon, France) and the department of periodontology of the Liège university hospital (Liège, Belgium). Patients will be included from March 2017 until December 2019.

Eligible patients are informed about the study by dentists and dental students working in the hospital. Then, a study investigator presents the study to patients and gives them information letters before inclusion. Ethical approval was obtained in both countries and patient consent is obtained and recorded in accordance with national regulations.

To be included in this trial patients must be 18 years old or over, be able to receive dental care, and be able to read, write, speak, and listen to French language. They must have at least 20 teeth including at least 4 permanent molars and 4 permanent premolars forming premolar-molar interdental sites. They must own an Internet-enabled smartphone or tablet, have an electronic mail address, agree to be registered in the automatic text messages contact system, agree to come to the two follow-up appointments, and be covered under the national health insurance system.

Exclusion criteria are history of periodontal treatment (end of treatment < 1 year), currently enrolled in a periodontal treatment program, last oral hygiene instruction and motivation < 1 year ago, last tooth scaling and polishing < 1 month ago, removable partial or complete dentures, fixed or removable orthodontic appliances, allergy to benzoic acid, under treatment by an antiplatelet or anticoagulant drug, hemophilia, unable to answer questions, unable to perform twice daily toothbrushing, unable to perform daily interdental care, using interdental brushes or dental floss more than once a week, under guardianship, legally deaf or blind, at risk of infectious endocarditis, and planning to relocate to another city during the duration of the study. Non-inclusion criteria have been chosen to reduce loss to follow up or unreliable results.

Medications taken by the patient less than 8 days before entering the study are recorded in the electronic case report form (e-CRF). History of or current renal condition, head and neck cancer, diabetes mellitus, current and past tobacco use, and other current medical conditions must be reported.

No special concomitant care or intervention is prohibited after inclusion in the trial. Patients are specifically instructed to use the material provided for this trial: electric toothbrush (Philips Sonicare, Philips Personal Health France, Suresnes, France); toothpaste (Meridol gum protection, GABA France, Colgate-Palmolive, Bois-Colombes, France); interdental floss (Inava DentoFil Black, Pierre Fabre Oral Care, Castres, France and Meridol expanded dental floss, GABA France, Colgate-Palmolive, Bois-Colombes, France); interdental brushes (Inava Monocompact and Inava Trio Compact, Pierre Fabre Oral Care, Castres, France and Elmex interdental brushes, GABA France, Colgate-Palmolive, Bois-Colombes, France).

### Sample size

A literature review found that behavioral interventions, similar to the patient education strategy explored in this trial, allow up to 15% reduction of dental plaque [21, 36–39]. However, to the best of our knowledge, there is no publication examining the eHealth concept for patient motivation for oral hygiene proposed herein. A conservative estimate of 10% reduction in PCR index was therefore chosen for the test group compared to the control group.

A total of 86 patients enables us to show a 10% difference in the PCR index between the two groups with 80% power, using a bilateral test with an alpha risk of 5%. At 8 weeks, 15% of patients are expected to be lost to follow up (calculated by nQuery Advisor 7.0) [40].

To encourage recruitment, the investigators organize regular communications with colleagues of the teaching hospitals, involve student representatives in the process by having them promote the study among their classes, and regularly have the study leaflet as the desktop image of computers in the relevant hospital departments. In addition, students who refer a patient for inclusion in the protocol receive extra points for their periodontology practical examination and the patient is referred back to them for the next phases of periodontal therapy.

### Randomization

Patients are randomized using a computerized and centralized system via a specific website. Patients are one-stage randomized, stratified on the following potential confounders: investigation center (Lyon versus Liège), patient gender (male versus female), and patient current tobacco status (currently a tobacco user versus not currently a tobacco user). Because all patient characteristics must be entered in the e-CRF before interventions are assigned, sequence concealment is secured.

### Implementation

The stratification algorithm was implemented by statisticians and methodologists independently of investigators. Patients are assigned to intervention arms by the center coordinator.

### Intervention

#### Visit 1

An investigator verifies the eligibility criteria at the first visit (T0). The patient is informed about the study both orally and by means of an information letter. Patient consent is sought and registered according to the national regulations. The patient’s inclusion is then formalized by the creation of a patient file in the e-CRF.

A clinical examination is performed to assess periodontal health and level of oral hygiene. Other oral conditions (such as dental caries, temporomandibular joint (TMJ) disorders, failing restorations, etc.) will be further treated by referrals inside the dental teaching hospital according to usual procedures and will not be considered in this study. Whenever clinically and ethically possible, the treatment of such conditions will be delayed for a maximum of 8 weeks until the end of the study in order not to interfere with the evaluation of periodontal parameters (e.g. reducing local plaque retention factors by repairing or replacing a failing filling). If treatment cannot be delayed, it will be recorded in the e-CRF.

Then, a 20-min MI session is conducted. All investigators apply the same structure of MI to all patients following a dedicated protocol available in the study folder. This MI protocol is arranged around five themes: reason for seeking consultation, dental and medical history, everyday consequences of periodontal or dental problems, current routine of oral hygiene, and knowledge of and willingness to obtain required dental and medical care. Such a framework was previously validated in a RCT and led to better results than patient instruction alone [36]. The patient is instructed and motivated for a tailored regimen of oral hygiene following international recommendations: twice daily electric toothbrushing with a toothpaste containing fluoride agents, the use of dental floss or interdental brushes, and adjunctive chemical plaque control agents if needed [11–13, 41–43]. Adjunctive chemical plaque control agents could be used for instance in the case of intense gingivitis, to help reduce the total bacterial load. Their use would be limited to as few patients as possible and for the shortest duration achievable [41], to reduce interference with results. If such agents must be used, it will be recorded in the e-CRF.

The use of an electric toothbrush, interdental brushes, dental floss, and toothpaste is demonstrated to the patients by investigators. The patient then has to demonstrate the use of these themselves and reinstruction is performed if needed. This MI session is provided to all patients, irrespective of their allocation (test versus control). All the required materials, including the electric toothbrush, are given to the patient during the MI session in sufficient quantity for the study duration. Patients are specifically instructed to use these tools, and only these tools, during the study. An electric toothbrush was chosen as a moderate level of evidence shows that they to lead to better plaque control and better gingivitis reduction than manual toothbrushes [43]. After the study, patients can keep all materials to continue using them. Replacement heads for the electric toothbrush, and refills for interdental brushes, floss, or toothpaste are readily available to the patients and at a relatively low cost. The end of the study should not prevent them from following the same oral hygiene routine in the long run if they so wish.

After the MI session, an outcome examiner conducts clinical data collection. The clinical data collection for the primary outcome is conducted using a dental plaque disclosing agent, with lip and OptraGate cheek retractors (Ivoclar Vivadent France, Saint-Jorioz, France), and under constant suction.

According to the manufacturer’s information, the TriPlaque disclosing agent (GC Europe, Leuven, Belgium) appears as different colors according to biofilm maturation; new plaque appears pink-red, mature plaque (present for > 48 h) blue-purple, extra high-risk plaque (pH < 4.5) appears light blue.

For data collection, the PCR index [44] is used with six sites per teeth (disto-buccal, buccal, mesio-buccal, mesio-lingual, lingual, disto-lingual). All colors are considered to indicate the presence of plaque and therefore the site is coded “1” by the outcome examiner. If no plaque is present, the site is coded “0”. The examination is conducted visually using loupes and a loupe-mounted light-emitting diode; during the examination a periodontal probe is used on the tooth surface with an aim to avoid false positives and false negatives.

The clinical examination for the secondary outcome is conducted immediately thereafter. A periodontal probe is used to assess the BOP index with six sites per tooth (disto-buccal, buccal, mesio-buccal, mesio-lingual, lingual, and disto-lingual). Criteria for the site to be coded “1” is bleeding within 30 s of probing [45], otherwise the site is coded “0”.

Then, the investigator records the personalized oral hygiene video. This video is recorded for all patients. The investigator uses a loupe-mounted miniature camera connected to a computer (Futudent Educam, Novocam Medical Innovations Oy, Helsinki, Finland). The video lasts approximately 3 min and displays the use of the electric toothbrush, the interdental brushes, and the dental floss. It contains audio instructions summarizing what was said to the patient during the consultation, and is to be watched while brushing the teeth.

After the video recording, the clinical part of the consultation is finished. Patients are then randomized by the center coordinator. Patients allocated to the control group are not given any further detail beyond their allocation. Patients allocated to the test group are registered in the text messages system and their personalized video is uploaded to the cloud portal by the investigator. The investigator instructs them on how the cloud portal and the text messages system work. Both the cloud portal and the text messages system are secured (see “Data management”, “Ethical considerations”, and “Discussion”). The cloud portable is accessible via any smartphone, tablet or computer with a web browser, irrespective of their operating system, and there is no need to install an application in an attempt to maximize technical compatibility. As no application is installed, no notifications will be used to remind the patient about watching the video: only text messages will be used.

The difference between control and test groups is the availability of the personalized oral hygiene video through the cloud server and the registration of the patient in the interactive text messages system. The two follow-up appointments are scheduled, and the visit is brought to an end. Patients in either of the two groups are not contacted by investigators between visits, except for administrative reasons such as rescheduling an appointment.

#### Text reminders

All text reminders sent to patients have the same structure: salutation, a piece of information on oral hygiene and oral health, a question as to whether the patient is compliant to the oral hygiene regiment that was prescribed, an invitation to view the oral hygiene video and a direct link to it, a recall of the date of the next appointment, greetings, and a link to opt out of the text reminder service (as required by law). The information on oral hygiene and oral health varies across messages, in an attempt to keep patients interested in the messages by avoiding repetition and providing them with new information. This piece of information is chosen in a randomized fashion, and once it has been used, it cannot be used in further messages.

Twelve messages are automatically sent during over the course of the study based on the following schedule: the day of visit 1 (V1), the day after V1, 2 days after V1, a week after V1, 2 weeks after V1, 3 weeks after V1, the day before visit 2 (V2), the day of V2, 1 week after V2, 2 weeks after V2, 3 weeks after V2, and 1 day before visit 3.

The patient can answer the text messages to tell the investigators if he is or is not adherent with the oral hygiene routine that was prescribed to him. To do that, he can reply to the text message he received. The system will register his answer in the database and initiate an automated reply. If the patient is adherent, the reply will include elements of positive reinforcement. If the patient is not adherent, the reply will attempt to play down the situation, reassure the patient and offer to discuss this issue at the next appointment. Enough messages have been written to ensure that they are never repeated. All interactions with the patient through text messages are registered in a database to allow descriptive analysis.

#### Visit 2

At the second visit (T0 + 4 weeks), patients are first asked to complete a self-administered electronic questionnaire about their motivation and behavior in terms of oral health [46] that is directly linked to the e-CRF and investigators are blinded to answers. Then, a short (< 5 min) recall about oral hygiene methods is proposed to the patient and conducted by the investigator if needed.

A brief clinical examination is conducted, and the outcome examiner then collects the clinical data. Data collection is conducted following the same protocol as for the first visit. Results are delivered to both the investigator and the patient, and are stored in both the e-CRF and the patient’s electronic healthcare records.

The investigator then conducts full-mouth supra-gingival and juxta-gingival tooth scaling and polishing (Acteon ultrasonic tip number 1 and Newtron LED handpiece, Satelec Acteon, Merignac, France). The investigator ensures thorough removal of calculus but avoids instrumenting the gingival pockets. Following completion of the scaling, patients are invited to rinse with a solution containing 0.12% chlorhexidine digluconate (Paroex, Sunstar France, Levallois Perret, France). Additional supplies of interdental brushes and floss are given to the patient if required. The next appointment is confirmed and the second visit is brought to an end.

#### Visit 3

At the third visit (T0 + 8 weeks), patients are first asked to complete the same questionnaire about their motivation for and behaviors in oral health they completed at the second visit. Then, a short (< 5 min) recall about oral hygiene methods is proposed to the patient and conducted by the investigator if needed.

A brief clinical examination is conducted, and the outcome examiner then collects the clinical data following the same protocol as for the first visit. Results are delivered to both the investigator and the patient, and are stored in both the e-CRF and the patient’s electronic health records.

At the end of the appointment, the patient is asked to complete a satisfaction questionnaire specially designed for dental care (Dental Visit Satisfaction Scale [47]). Again, data are directly entered by the patient into the e-CRF and investigators are blinded to the answers.

Participation of the patient in the study is complete at the end of the third visit. Should the patient require further treatment, they are referred to the relevant departments following standard hospital protocols. If the patient does not need further treatment, they are informed that they should seek an appointment in 1 year for a check-up, either with the staff of the dental teaching hospital or with another dental care provider. The possibility to consult with another dental care provider is by law an inalienable right of the patient. The Ethics Committee emphasized that the patient should be reminded of this.

Various strategies are implemented to improve adherence to intervention protocols: the investigators follow dedicated written protocols to structure the MI (T0), to harmonize the oral hygiene videos (T0), and for recalls about oral hygiene (T0 + 4 weeks and T0 + 8 weeks).

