### Outcome measures

Data collection is performed by three blinded, independent, calibrated outcome examiners at 0, 4, and 8 weeks after patient inclusion. For the primary objective (oral hygiene) and the main secondary objective (gingival inflammation) the outcome will be the value of indices collected during the third visit (8 weeks of follow up). Values range from 0 to 100%.

Two additional secondary objectives will be also considered: patient satisfaction after 8 weeks, and patient motivation for change after 4 and 8 weeks in each treatment arm. For the first secondary objective (patient satisfaction after 8 weeks), the Dental Visit Satisfaction Scale questionnaire [47] comprises 10 multiple choice questions (MCQ) scored on a 5-point Likert scale, and explores three aspects of patient satisfaction: information-communication, understanding-acceptance, and technical competence (Additional file 1). For the second secondary objective (patient motivation for change after 4 and 8 weeks), a questionnaire featuring 12 questions (MCQ or binary) derived from previous publications is used [46] (Additional file 2). Results from this questionnaire would allow a preliminary understanding of psychological factors predictive of patient motivation and readiness to change behavior.

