The choice of a given plaque index has an impact on the statistical analyses - and likely on the outcomes. Several plaque indices have been developed, with different fields of application [60]. The modified PCR index chosen for this study records presence or absence of plaque (binary outcome) on six sites per tooth. Some indices are more research-oriented such as the Turesky modification of the Quigley-Hein Plaque Index that records plaque as an ordinal outcome with six levels [61, 62] or the Rustogi/Navy Plaque Index that records plaque still as a binary outcome but on nine sites per tooth [63]. An ordinal outcome and more sites per tooth dramatically increase the sensitivity of the index, thus allowing the detection of smaller differences between groups [64, 65]. While the original PCR index proposed by O’Leary et al. used four sites per tooth [44], it was decided for this RCT to use six sites per tooth to achieve a balance between clinical practicability and precision for plaque assessment. Also, using a plaque disclosing agent facilitates the detection of plaque [66] but a number of false positives were detected during the calibration phase of the trial. Taking this finding into consideration, outcome examiners were instructed to use a periodontal probe on the tooth surface when in doubt, to clear any uncertainty about the presence or absence of plaque.

In terms of internal validity, the sources of bias are limited by the use of centralized randomization (selection bias), strict prospective data record and monitoring (information bias), and blinded outcome examiners (performance and detection bias). However, because of the nature of the investigation, the patients cannot be blinded. Also, investigators are not blinded but as patients are randomized at the end of the first visit, it ensures that investigators are not biased when performing the MI and recording the video.

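### At visits 2 and 3 a discretionary oral-hygiene recall by an unblinded investigator comes before plaque and bleeding are scored, which leaves an avoidable route for bias of unknown size and direction

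*Protocol article*

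**What the plan says.** The Visit 3 section (Methods, Intervention) gives this order: patient questionnaire, then a short "recall about oral hygiene methods is proposed to the patient and conducted by the investigator if needed", then "A brief clinical examination is conducted, and the outcome examiner then collects the clinical data following the same protocol as for the first visit". The Visit 2 section has the same order. Under Outcome measures, for the primary and the main secondary objective, "the outcome will be the value of indices collected during the third visit (8 weeks of follow up". The visit 3 scores are therefore the trial's main endpoints.

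Under Trial design, "only outcome examiners and data analysts are blinded to the allocated intervention". The Discussion confirms that "investigators are not blinded but as patients are randomized at the end of the first visit", and uses that timing to defend the motivational interview and the video recording. It also credits "blinded outcome examiners (performance and detection bias" among the safeguards.

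Three other statements matter. The end of the Visit 3 section says that investigators follow a written protocol for the recalls at 4 and 8 weeks. The Visit 1 section names video access and text-message registration as the difference between the groups, so the recall is not an arm-specific component. Under Text reminders, the automated reply to a test patient who reports non-adherence will "offer to discuss this issue at the next appointment".

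**The concern.** The primary endpoint is meant to reflect eight weeks of home care. Placing a recall between the patient's arrival and the scoring allows something done in the chair to enter that measurement. The person giving it knows the arm, and the need for it is judged after randomization.

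Unequal use is plausible without any misconduct, and it could go either way. If the eHealth package works as hypothesized, control patients may need the recall more often, which would shrink the observed difference. Conversely, only test patients are asked about adherence by text and offered a discussion at the visit, which could raise recall use in the test arm and enlarge the difference.

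The safeguards named in the Discussion do not reach this step. Randomizing at the end of visit 1 protects what happened before it. A blinded examiner scores without knowing the arm, but cannot undo a change made to the mouth a few minutes earlier.

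Visit 2 matters less but is not irrelevant. Its scores feed the last-observation-carried-forward sensitivity analysis, and even a verbal recall there could influence the following four weeks.

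**Working it through.** **The plan's own figure.** The Sample size section gives 86 patients, a 10-point PCR difference, 80% power, two-sided alpha 5% and 15% loss. It gives no SD, so 86 can only be solved backwards, with n per arm = 2(1.96 + 0.84)² SD² / 10².
- SD 15: 36 per arm, 72 in total, and 72/0.85 = 85 after allowing for loss. The t-test version gives 37 per arm, 74, then 88. An SD near 15 therefore fits if 86 includes the loss.
- SD 16.25 (t test) or 16.5 (normal approximation): 43 per arm, 86 in total. This fits if 86 is before loss.

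The point does not depend on which is right. The SD is used only to scale the illustration.

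**What the text settles**
1. The recall comes before scoring at visits 2 and 3: stated.
2. The person giving it is unblinded: stated.
3. It is given only where needed, so not every patient receives it: stated. Who judges the need is not stated.
4. It is available to both arms and has a written protocol: stated.
5. It involves cleaning in the mouth: not stated. Hands-on use of the tools by the patient is described only for visit 1, where it precedes randomization and applies to everyone.
6. It is used more in one arm: not stated.

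Items 1 to 3 open the route. Bias needs both 5 and 6.

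**Illustration.** Bias = (PCR points removed by a recall) × (difference between arms in the share given one). Neither input is in the documents; both are assumed. Further assumptions are a true difference of 10 points, SD 15 and 43 × 0.85 ≈ 36.5 evaluable patients per arm. The standard error is 15 × √(2/36.5) = 3.51. The power column takes the control arm as recalled more often. The last column applies in either direction.

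| Points removed | Difference in share | Bias | Power | Type I error if no true effect |
|---|---|---|---|---|
| 0 (verbal), or equal use | any / 0 | 0 | 81% | 5% |
| 5 | 0.10 | 0.5 | 77% | 5% |
| 10 | 0.20 | 2 | 63% | 9% |
| 20 | 0.30 | 6 | 21% | 40% |

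For the third row, (10 − 2)/3.51 − 1.96 = 0.32, which gives power of about 63%. With SD 16.25 and 43 per arm, the powers in the last three rows are nearly the same (77%, 63% and 21%).

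**The case against.** The strongest reply is that the harm is assumed. The article describes a recall of under five minutes about methods. A verbal reminder removes no plaque and provokes no bleeding. The recall is available to both arms under a written protocol that a condensed article need not reproduce, and that protocol may settle both its content and the criteria for giving it. The text-message offer is part of the package under test, and nothing says that a reply triggers a recall. All of this stands, and it is why no bias can be claimed as established.

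Four stronger readings are tempting and are not supported:
- A reader might infer that the recall is an arm-dependent co-intervention. The documents show only that its use could differ by arm.
- A reader might infer that it does alter plaque minutes before scoring. That needs cleaning in the mouth, which is not described for visits 2 or 3.
- A reader might infer that equal use would still compress the contrast. Removing the same number of points in both arms leaves the difference unchanged. Compression needs removal proportional to the plaque present, or a floor effect, and neither is documented.
- A reader might infer that the article claims its randomization timing covers the later recalls. It claims this only for the interview and the video.

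A last objection is that reordering during the trial mixes two measurement conditions. This is a small cost, because the order changes in both arms alike and can be dated.

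What the reply does not remove is the stated sequence. A written protocol can standardize content, but as described delivery remains conditional on need, and no stated safeguard separates the recall from the scoring.

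**Conclusion.** The concern holds as an avoidable weakness in the order of procedures. A recall whose delivery is decided after randomization, and which is given by an unblinded investigator, precedes the primary measurement, and examiner blinding does not close that route. Whether any bias follows is unknown. It is zero if the recall is verbal or equally used. On the assumed inputs it reaches about 6 points of the 10-point target if the recall is hands-on and used unevenly. The direction is also unknown, and without a record of who received a recall the effect could not be examined afterwards. The sequence is certain from the text; the size is illustration only.

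The change is still worth making. Participation ends at visit 3, so a recall given before scoring there adds nothing to the eight weeks of home care being measured.

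**What to change.** - At visits 2 and 3, have the blinded examiner score PCR and BOP before any recall. Keep the recall itself as planned, after scoring.
- Record in the e-CRF whether a recall was given at each visit, and report it by arm. Include, as far as records allow, recalls already given before scoring.
- State from the written recall protocol whether any cleaning in the mouth takes place. If none does, saying so removes the immediate concern for patients already scored.

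The cost is a reordering within the same visit and one e-CRF item, with no added staff or procedures. There are three side effects to note:
- Patients seen before the change were scored under the old order, so its date should be recorded. The article describes recruitment as ongoing, but inclusion was due to close in December 2019, the month of publication. For many patients only the recording and reporting may still be possible.
- Baseline was scored after the visit 1 demonstration, so baseline and follow-up conditions would differ. This is the same in both arms, and baseline enters only as an adjustment.
- At visit 2 the scores could be known before the recall is offered, which might influence who receives one. The e-CRF item would show any imbalance.
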